### Sample size

Sample size for the primary outcome was calculated using estimates of effect sizes from (i) a meta-analysis of exercise training interventions and (ii) an randomized clinical trial based on a behavioral intervention for middle-aged patients with hypertension, evaluated by ambulatory BP monitoring, and analyzed in an intention-to-treat approach [7, 28]. We estimated that 184 participants would provide power values of 0.79 and 0.92 to detect differences of 2.5 mmHg and 3.0 mmHg between the two group mean values for the 24-h systolic BP, with an expected standard deviation of 6.0 mmHg. Such power calculation comprises: (1) an excess of 22 subjects due to the expected dropout rate (10–15%), (2) intraclass correlation of 0.1 in order to account the proportion that the center-to-center variance may affect the response variance, and (3) a two-sided significance level of 0.050 obtained from a mixed effects model fit without the treatment-by-center interaction.

### Recruitment

The recruitment period for the HAEL Study is planned to range from September 2017 to March 2019. Recruitment phase began from September 2017 to December 2017. During this period, screening questionnaire was administered to 111 individuals (98 of those were not included due to exclusion criteria) and the total enrollment comprised 13 individuals. This was the initial phase to implement the processes for trial conduction in both centers.

From January 2018 on, we have established recruitment targets by center for participant inclusion.

To accomplish such targets, a multifaceted approach is used according to each center resources and comprises screening of electronic medical records as well as advertising means based on recruitment-billboards, newspaper releases, e-flyers in social media, word of mouth, and personal references. In addition, we developed a web site for the HAEL Study (www.ufrgs.br/hael) by which we present study relevant information and contact details. All communication and publicity materials have received IRB approval.

### Assignment of interventions and blinding

Once included in the study, the participant receives an internal number to be de-identified. Sequence of allocation is based on computer-generated random numbers (www.random.org; randomness via atmospheric noise), 1:1 ratio, with permuted blocks of random sizes that are not disclosed to ensure concealment. Allocation concealment is implemented through a central randomization routine conducted by investigators with access to the randomized list (list holders: [name], [name], [name]) and investigators charged with requesting the code to place subjects to their intervention group. In brief, assigners fill an online request whenever one or more subjects should enter an intervention arm. Thereafter, one of the list holders consult the code in consecutive order and uncover the code relative to the requested subject(s). Such requests are documented and archived for further accountability. To ensure intervention blinding, communication with participants is not carried out by the investigators involved in outcome assessments.

Blinding is implemented for outcome assessors and data analysts (double masking) of primary and secondary outcomes listed in this protocol. Due to the nature of interventions, the study staff conducting or supervising exercise or educational sessions as well as participants are not blinded. To ensure masking of the assessor, subjects are asked to omit their assigned group and not to talk about their interventions during outcome evaluation sessions. In the case of unintentional unblinding due to any reason, it is mandatory for involved researchers to notify the center coordinator. In such cases, participant ID, date, and unblinding circumstance are documented for internal control.

### Data collection

A manual of operating procedures (MOP) was written to increase the consistency for implementation of assessments and interventions across the two study centers. In addition, standard operating procedure (SOP) documents are available for each assessment. Outcome assessors were trained and the handling of a SOP short version is mandatory during each data collection. A data collection committee formed by members of the two centers gathered before the trial onset to consolidate data collection procedures between centers. Periodic meetings and written communication are established to promote internal transparency and consistency.

All variables are assessed at baseline (prior randomization) and at study completion, whereas endothelial function, self-reported physical activity and handgrip strength are additionally assessed at the 6th week of intervention. A participant timeline for the study is presented in Table 3.

#### Measurement of primary outcome

##### Ambulatory BP

In the assessment of 24-h BP, subjects wear an ambulatory BP monitor (90,207, SpaceLabs, Redmond, WA, USA) on the non-dominant arm for 24 h. Participants are asked to refrain from exercise the day prior to and during the recording period. While wearing the monitor they are also asked to maintain a diary of daily activities to record any abnormal activities (such as highly stressful situations, increased physical exertion, etc.) and sleep hours. Data on self-reported sleep times will be used to analyze daytime and nighttime patterns of ambulatory BP monitoring. Ambulatory BP exams are considered valid when at least 70% of the expected readings are available, otherwise, an additional measurement is necessary [29]. Subjects allocated to the combined training intervention undergo the ambulatory BP assessment at least 24 h and no later than 10 days after the last exercise session.

#### Measurements of secondary outcomes

##### Office BP

After sitting the subjects in a calm environment for 5 min, a researcher measures the subject’s BP using calibrated and automated oscillometric devices (OMRON Healthcare Inc., Bannockbur, IL, USA), according to hypertension guidelines [30]. Three measurements, 1–2 min apart, are performed in the arm with the highest initial value. The average of the three measurements is considered the subject’s office BP.

##### Cardiorespiratory fitness

Subjects undergo a maximal cardiopulmonary test on a treadmill. Rates of oxygen uptake, carbon dioxide and volume of expired air are recorded breath-by-breath during an incremental walking/running protocol, with VO_2_peak determination when criteria for test termination is reached [31]. All tests are supervised by a trained exercise physiologist and a physician, using a ramp protocol with rate of increments (both speed and elevation) implemented at their discretion, based on participants’ clinical history, aiming a test lasting from 8 to 12 min. Subjects are asked to take their medications normally and refrain from caffeine consumption prior testing. Due to different gas analyzers between study centers (Porto Alegre: Cortex Metalyzer 3B, Leipzig, Germany; Pelotas: VO2000 MedGraphics, Ann Arbor, MI, USA, respectively), VO_2_peak average values and CI 95% will be checked at the study completion. If a difference is identified between centers, VO_2_peak will be reported accordingly.

##### Walking distance

Subjects undergo a six-minute walking test conducted in a flat 30 m course, in which the total distance walked “as fast as possible” is assessed. Researchers are not allowed to give verbal encouragement other than standardized neutral cues each minute.

##### Lower limbs functional capacity

Subjects complete the SPPB which is a 3-step testing that assesses balance, walking speed, and lower limbs muscular endurance [32, 33]. The balance stage of the test is comprised of three balance challenges of increased difficulty. The walking speed test assesses the 3-m regular-pace walking speed. The muscular endurance assessment involves standing-up five times from a chair as fast as possible without using the arms. The final test score is calculated as a sum of the scores obtained in the three tests. Each test has a maximum score of 4 points.

##### Geriatric depression symptoms

Participants are asked to complete a version of the Geriatric Depression Scale 15 (GDS-15) validated for Brazilian Portuguese [25]. This questionnaire is comprised of 15 questions and is validated to assess depressive symptoms in the Brazilian elderly population. Due the personal nature of the provided information, questionnaires are answered by the participant alone and assisted by researchers only if needed.

##### Quality of life

Participants answer the WHOQOL-OLD questionnaire, translated and validated forBrazilian elderly population [26]. This questionnaire is comprised of24 questions and is an estimate for QoL in 6 different domains. As justified in the procedure above, questionnaires are answered by the participant alone and researchers provide help only if requested.

##### Autonomic function

Autonomic function is assessed by BP and heart rate variability (MP150, Biopac Systems, USA). Phalangeal beat-to-beat BP is recorded (in a sampling rate of 1000 Hz) at supine rest for 10 min and during a 5-min application of a variation of the Stroop Color- Word Conflict test [34]. This test is a mental stress challenge to sympathetically stimulate the subjects. We calculate the BP and heart rate variability based on a spectral analysis of systograms and tachograms. This method provides three frequency band components (Very Low Frequency, Low Frequency and High Frequency) from which autonomous control can be inferred.

##### Endothelial function

To determine the flow-mediated dilatation (FMD), longitudinal images are obtained with the use of high-resolution ultrasonography (HD7XE, Phillips, USA). To do so, a high frequency transducer (3-12 MHz) records the dilatation of the brachial artery for 120 s immediately after the release from a 5-min total occlusion maneuver. The subjects are asked to fast for at least 6 h prior to the procedures. Brachial Analyzer Software (Vascular Tools, Medical Imaging Application, USA) is used to quantify changes in arterial diameter from baseline to post-cuff occlusion. Flow-mediated dilation will be calculated as the percentage change in arterial dimeter fromaverages of 10 baseline diastolic diameters and 3 maximum, systolic diameters post-cuffocclusion. In addition to the pre-and post-trial measurements, a mid-term FMD assessment is conducted during the 6th week of intervention.

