#### Main secondary outcomes

A set of secondary outcomes clinically relevant for the elderly populations was established, including diastolic BP, endothelial function, and cardiorespiratory fitness. Together with systolic BP, the diastolic BP will be assessed through ambulatory and ‘at office’ measurements. Endothelial function is determined by flow-mediated dilatation measured by high resolution ultrasonography at baseline, mid-intervention (6 weeks), and post-intervention (12 weeks), in agreement with published guidelines [17]. Due to resource availability, this outcome is assessed only in participants allocated at the coordinator center. Cardiorespiratory fitness is determined by peak oxygen consumption (VO_2_peak) obtained by maximal cardiopulmonary exercise testing at baseline and 12 weeks. Data regarding both main secondary outcomes will be aggregated as group means at the measurement timepoints.

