### Data management

At the two study centers, data are collected on standardized paper forms identified by subject number and trial ID and containing instructions for standardized operational procedures. From these forms, we proceed with double data entry for primary, secondary, and additional outcomes. Data entry is carried out at each study center, however, data are centrally stored and managed through the use of REDCap electronic data capture tools hosted at the Hospital de Clínicas de Porto Alegre. REDCap (Research Electronic Data Capture) is a secure, web-based application that will provide us with (1) an intuitive interface for validated data entry; and (2) audit trails for tracking data manipulation and export procedures [36]. Audition for missing or inaccurate data is conducted at the coordinator center. Data are backed up daily by automated export procedures from secure servers of the Hospital de Clínicas de Porto Alegre.

In addition, brachial artery images for endothelial function assessment will be analyzed at an external laboratory (Cardiovascular Aging Research Laboratory, Austin, Texas). To do so, we will share image files over a secure cloud-based sharing platform (Box Inc., USA) hosted by the University of Texas at Austin.

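### Flow-mediated dilation is defined from a diastolic resting diameter to a systolic post-occlusion diameter, so the reported value includes within-beat pulsation as well as endothelial dilation

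*Protocol article*

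**What the plan says.** The Main secondary outcomes section lists a set of outcomes "including diastolic BP, endothelial function, and cardiorespiratory fitness". Endothelial function is measured by brachial artery ultrasound at baseline, 6 weeks and 12 weeks. The same section adds that "this outcome is assessed only in participants allocated at the coordinator center" and describes the measurement as "in agreement with published guidelines".

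The operational definition is in the Endothelial function section: "Flow-mediated dilation will be calculated as the percentage change in arterial dimeter", taken from averages of "10 baseline diastolic diameters and 3 maximum, systolic diameters" after cuff release. The post-release recording lasts 120 seconds. The article gives no other FMD formula, no same-phase alternative, and no adjustment of FMD for blood pressure or pulse pressure.

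Under Data management, "brachial artery images for endothelial function assessment will be analyzed at an external laboratory", with the image files shared electronically.

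**The concern.** Within each heartbeat the brachial artery is wider in systole than in diastole. If the resting diameter is diastolic and the post-occlusion diameter is systolic, their ratio contains the ordinary pulsation of the vessel as well as its response to the increased flow. An artery with no endothelial response would still score above zero.

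The extra part depends on pulse pressure and on wall stiffness. The trial's main hypothesis is that exercise lowers systolic ambulatory blood pressure, and the Discussion expects vascular adaptation. The reported outcome therefore contains a component that the intervention might change by a route other than endothelial function. FMD is a main secondary outcome with a superiority hypothesis, so its definition should measure what its name says.

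**Working it through.** **Inputs from the protocol article.** Diastolic diameters at rest, systolic diameters after occlusion, percentage-change scale (Endothelial function); three visits, coordinator center only (Main secondary outcomes); design differences of 2.5 and 3.0 mmHg in 24-h systolic BP (Sample size). The article gives no expected FMD, SD or power for FMD, so there is no stated figure to reproduce.

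**Assumed inputs.** True same-phase dilation f = 4%; within-beat distension p (systolic over diastolic diameter, minus 1) between 1% and 5%. Neither is in the document.

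**Step 1: the level.** Let D be the resting diastolic diameter. The post-occlusion diastolic diameter is D(1+f) and the systolic one is D(1+f)(1+p). The formula as written gives

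reported FMD = (1+f)(1+p) − 1 = f + p(1+f).

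| p (assumed) | f = 0% | f = 4% |
|---|---|---|
| 1% | 1% | 1.04 × 1.01 − 1 = 5.04% |
| 2% | 2% | 1.04 × 1.02 − 1 = 6.08% |
| 3% | 3% | 1.04 × 1.03 − 1 = 7.12% |
| 5% | 5% | 1.04 × 1.05 − 1 = 9.20% |

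With one phase at both time points, p drops out and the result is f: 0% and 4%.

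**Step 2: the contrast when p is the same in both arms.** The difference in reported FMD is (1+p)(f_exercise − f_control). The pulse term cancels and leaves a scale factor of 1.01 to 1.05. If the true responses are equal, the reported difference is zero.

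**Step 3: the contrast when p changes differently.** With equal f in both arms, a between-arm difference dp in the change of p produces a spurious difference of (1+f) × dp. For f = 4% and a relative fall in p in the exercise arm only:

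| p (assumed) | 10% relative fall | 20% relative fall |
|---|---|---|
| 1% | −0.10 points | −0.21 points |
| 3% | −0.31 points | −0.62 points |
| 5% | −0.52 points | −1.04 points |

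**Step 4: a scale for the blood pressure route alone.** Assume a pulse pressure of 50 to 70 mmHg (not in the document), diastolic BP and stiffness unchanged, and p proportional to pulse pressure. The design differences then lower pulse pressure by 2.5/70 = 3.6% to 3.0/50 = 6.0%. The spurious difference is 1.04 × 1% × 0.036 = 0.04 points to 1.04 × 5% × 0.060 = 0.31 points, against exercise. A fall in diastolic BP as well would make it smaller. Lower wall stiffness would raise p and act in the opposite direction.

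**The case against.** The strongest reply is that randomization already deals with most of this. The increase from 4% to as much as 9.2% affects the level of FMD, not the treatment effect, and Step 2 shows that a constant p leaves the contrast almost unchanged. That stands. A reader might take the level inflation as the size of the bias between arms, but the formula does not support that.

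A reader might also infer that the FMD result is confounded with blood pressure, or tilted towards exercise. Neither follows. Allocation is random, so the issue is contamination of a measurement by a component that depends on BP and stiffness. The BP route would work against exercise and the stiffness route for it, so the net direction is unknown.

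Nor can it be said that the pulse component could never be removed later. Image files go to an external laboratory for analysis, so a same-phase reading should remain possible.

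Finally, the sentence may be a slip. The article claims agreement with published guidelines, which cannot be checked here, and the Data collection section says a separate operating procedure exists for each assessment. The laboratory may already read one phase, so a flaw in the actual readings is not established. But a general citation does not override an explicit formula, and this is the only one given. It needs correcting or confirming in either case.

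**Conclusion.** The FMD definition is wrong as written. It mixes cardiac phases, so the reported value is f + p(1+f) and not f. That part is algebra and rests only on the artery being wider in systole than in diastole.

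The size rests on assumptions. For f = 4% and p of 1% to 5%, the level is reported as 5.0% to 9.2%. Bias in the between-arm contrast is about (1+f) times any differential change in p, and is zero if there is none. Such a change is plausible because the intervention aims to lower systolic BP and may alter the vessel wall, but the document fixes neither its size nor its sign. The figures in Steps 3 and 4 are illustrations, not estimates.

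The consequence is confined to one main secondary outcome at the coordinator center. The primary outcome, 24-h systolic BP, and its sample size are unaffected. The point still deserves correction because the remedy is cheap and removes the pulse term.

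**What to change.** State in the protocol, and in the reading instruction to the external laboratory, that resting and post-occlusion diameters are taken at the same point of the cardiac cycle, for example both end-diastolic, and compute percentage FMD from those. Apply this identically to the image files from all three visits before unblinding. If mixed-phase readings already exist, keep them as a supplementary analysis only. If the laboratory already reads one phase, correct the sentence to say so.

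The cost is a changed instruction and re-reading of any clips already measured. This assumes that the stored post-release recordings include the chosen phase, which the laboratory can confirm. No new visits or participants are needed, and the primary analysis does not change.

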#### Control variables

##### Anthropometric assessment

The subject is weighted on a calibrated scale, with light clothes and no shoes. Height is assessed through an analogic stadiometer, during a light inhale and with the head positioned in the Frankfurt plane. Waist circumference is assessed in the midpoint between the iliac crest and the 10th rib.

##### Adherence to pharmacological plan

Subjects answer a validated Brazilian version of the MMAS-8 [20–23], which is comprised of eight self-reported items related specifically to adherence to anti-hypertensive medication scheme. This scale’s score is divided into three categories: high adherence, moderate adherence and low adherence.

##### Blood variables

Blood samples are collected for quantification of total cholesterol, HDL-cholesterol, creatinine, and glycated hemoglobin (HbA1c). In brief, after 12 h of fasting, an experienced technician collects 4 mL of blood from the antecubital fossa. In the coordinator center, blood samples are taken directly to the clinical pathology laboratory (central laboratory) where they are centrifuged and subsequently analyzed. In the participant center, blood samples are centrifuged and stored in a − 80 °C freezer. After 10–20 participants are sampled either at t0 or t5 (Table 3), the samples are transported in a thermic container filled with dry ice to the central laboratory for analysis.

##### Physical activity levels

subjects answer a validated Brazilian version of the IPAQ [35]. The IPAQ long version is used, which assesses physical activity in five independently domains, namely: (a) job-related, (b) transportation, (c) housework, (d) recreational and (e) time spent sitting.

##### Handgrip strength

isometric handgrip strength is measured in both arms with an analogic hand dynamometer (Jamar Sammons Preston Rolyan, Bolingbrook, IL, USA). After one research team member demonstrates proper device and body positioning, the subject keeps an upright standing posture and position his/her evaluated arm with the forearm parallel to the ground (elbow flexed at 90°). Thereafter, the subject is instructed to perform a maximal squeezing contraction with sustained (isometric) effort lasting 5 s. Three attempts are carried out in each arm with one-minute rest intervals.

### Adherence assessments

Measures of adherence to interventions will be reported as group averages and operationalized as attendance and compliance. Attendance is monitored through session’s frequency recording and will be treated as the percent of intervention sessions experienced by a participant given the total number of scheduled sessions (36 sessions for the exercise program or 12 sessions for the education program). Adherence will be treated as the percent of intervention sessions fully accomplished without protocol deviations given the total number of scheduled sessions. For example, this may include either: (i) a participant allocated to the exercise program that, for any reason, walked less than the prescribed duration for a given session; or (ii) a participant allocated to the education program that only partially watched a lecture.

### Data management

At the two study centers, data are collected on standardized paper forms identified by subject number and trial ID and containing instructions for standardized operational procedures. From these forms, we proceed with double data entry for primary, secondary, and additional outcomes. Data entry is carried out at each study center, however, data are centrally stored and managed through the use of REDCap electronic data capture tools hosted at the Hospital de Clínicas de Porto Alegre. REDCap (Research Electronic Data Capture) is a secure, web-based application that will provide us with (1) an intuitive interface for validated data entry; and (2) audit trails for tracking data manipulation and export procedures [36]. Audition for missing or inaccurate data is conducted at the coordinator center. Data are backed up daily by automated export procedures from secure servers of the Hospital de Clínicas de Porto Alegre.

In addition, brachial artery images for endothelial function assessment will be analyzed at an external laboratory (Cardiovascular Aging Research Laboratory, Austin, Texas). To do so, we will share image files over a secure cloud-based sharing platform (Box Inc., USA) hosted by the University of Texas at Austin.

